### Assessment

Participants will undergo a thorough assessment using well-validated measures of mental health, biological samples analyses and physical health screening administered by trained research assistants and nurses. Most of the proposed measures have been employed in previous research and have good psychometric properties. These measures will have both English and Mandarin versions.

At baseline, socio-demographic data (such as age, gender, education and previous occupation), medical information, family history and lifestyle factors (such as gardening habits and frequency of park visits) will be obtained via a structured questionnaire. All baseline assessments will be completed in the 3 weeks before commencement of intervention.

#### Measures of mental health

Mental health is defined both in terms of psychopathology as well as positive well-being.Depressive and anxiety symptomatology of older adults will be measured by the Zung Self-Rating Depression Scale (SDS) and the Zung Self-Rating Anxiety Scale (SAS).
The SDS [25] is a 20-item quantitative measurement of symptoms of depression. Participants rate each item regarding how they felt during the week preceding using a 4-point scale that ranges from 1 (*a little of the time*) to 4 (*most of the time*). The higher the total score, the greater the severity of depressive symptoms. Several studies have established the SDS as a reliable and valid instrument for measuring depressive symptoms in Singaporean Chinese [26].The SAS [27] will be used to measure anxiety of the participants in the preceding week. It is a 20-item self-report assessment designed to measure anxiety levels, based on cognitive, autonomic, motor and central nervous system symptoms. Each question is scored on a Likert-type scale of 1–4 (*a little of the time*) to (*most of the time*). Some questions are negatively worded to avoid the problem of set response. Overall assessment is done by total score. The total raw scores range from 20 to 80, with higher score indicating a greater severity of anxiety symptoms.
(2)Well-being will be assessed by the following instruments:
The Ryff Scales of Psychological Well-Being [28] is an 18-item questionnaire which reflects the six areas of psychological well-being: autonomy, environmental mastery, personal growth, positive relations with others, purpose in life, and self-acceptance. Respondents rate statements on a scale of 1 to 6, with 1 indicating strong disagreement and 6 indicating strong agreement.In measuring, life satisfaction, the Satisfaction with Life Scale (SWLS) will be administered [29]. SWLS is a 5-item scale designed to measure global cognitive judgments of one’s life satisfaction (not a measure of either positive or negative affect). It is a psychometrically sound measure [30] and has been validated in a geriatric population [29]. Participants indicate how much they agree or disagree with each of the 5 items using a 7-point scale that ranges from 1 (*strongly disagree*) to 7 (*strongly agree*). Total scores range from 5 to 35, with higher scores indicating higher level of life satisfaction.The 6-item Friendship Scale [31] will be administered to measure both social isolation and social connectedness. Participants were asked to rate the frequency in which each statement describes them during the past four weeks on a 5-point Likert scale ranging from 0 (*almost always*) to 5 (*not at all*). Total scores range from 0 to 24, with higher scores indicating higher level of social connectedness. The scale was validated with older adults with excellent internal structures, reliability (α = 0.83) and validity [31, 32].In order to gather biological evidence to collaborate with the self-report measures of psychological well-being, the immunology status of participants will be investigated via pro-inflammatory cytokines including Interleukin 6 (IL-6), Interleukin-1 beta (IL-1β), C-reactive protein (CRP), Cortisol, Brain-derived neurotrophic factor (BDNF) and Dehydroepiandrosterone sulphate (DHEAS). Venipuncture will be carried out by qualified research nurses at the research centre. Venous blood (10 ml) will be collected in cell preparation vacuum tubes with sodium citrate (BD plastic vacutainer #362761) for collection of Plasma and Peripheral Blood Mononuclear Cells (PBMC). Samples will be delivered and processed within 3 h after the first venepuncture of the morning, which will be performed at room temperature. Once the samples arrive at the laboratory, 100ul of whole blood, for flow cytometry staining, will be aliquoted into Trucount tube. Subsequently, centrifugation of the samples will be performed at 1650 g, for 25 min at room temperature.After centrifugation, plasma will be aliquoted into several sterile 15 ml tubes. Subsequently, PBMC will be re-suspended, transferred into a sterile 15 ml tube and topped up with cold sterile Phosphate-buffered Saline (PBS) and 5% Fetal Bovine Serum (FBS). PBMC will be centrifuged at 1500 rpm for 5 min at 4°C. 500,000 PBMCs will be aliquoted into 2 ml Eppendorf tubes, processed and lysed in 600ul of miRVana Lysis buffer for downstream deoxyribonucleic acid/ ribonucleic acid (DNA/RNA) extraction. Remaining PBMCs will then be further processed, re-suspended in 90% FBS and 10% Dimethyl Sulfoxide (DMSO) and stored in cryovials. All samples will be stored at −80°C until required. Biobanking will be in liquid nitrogen.

#### Assessment of cognitive functioning

A battery of performance-based neurocognitive tests which evaluates across various cognitive domains including attention, learning, memory, visual-spatial skills and executive function will be administered by trained research assistants. This test battery has been adapted in local population with proved sensitivity in picking up differences with relatively small effect size [33, 34]. Clinical Dementia Rating (CDR) [35] is semi-structured, informant-based clinical interview which is rated based on a 5-point scale which characterize six domains of cognitive and functional performance applicable to Alzheimer disease and related dementias: memory, orientation, judgment & problem solving, community affairs, home & hobbies, and personal care. It has demonstrated convergent validity and discriminatory ability in the local population.The Montreal Cognitive Assessment (MoCA) [36] will be administered as global measures of cognitive function. MoCA is a brief screening tool for Mild Cognitive Impairment and Alzheimer Disease and was shown to have higher diagnostic accuracy and sensitivity to cognitive decline than the widely used Mini-Mental State Examination [22] and has been validated in the local population [37].Rey Auditory-Verbal Learning Test (RAVLT) [38] that evaluates immediate and delayed recall, learning rate, recognition, proactive and retroactive interference, primacy and recency will be administeredDigit Span Task [39] that assesses attention and verbal working memory will be administered.To assess for sustained attention and sequencing, Colour Trails Tests [40] will be conducted.In measuring visual-spatial and organizational processing abilities, as well as non-verbal problem-solving skills, Block Design [39] will be administeredSemantic Verbal Fluency (Animals) which taps on lexical knowledge and semantic memory organization will also be administered.

#### Assessment of physical health

A basic health screening of blood pressure, pulse rate, height and weight will be measured to investigate the effects of the therapy on physical health of the participants.

### Qualitative data

Feedback questionnaire will be conducted to solicit participants’ subjective experience and thereby expanding our understanding of the impact of the HT intervention. The survey will ask participants to identify what was the most helpful part of the class, what suggestions they have for improvement, and whether they had continued gardening and/or visiting the parks. This brief survey will only be administered once during the post-intervention assessment. Participants’ responses will be informally tallied and listed in categories.

### Sample size

For a pilot RCT with continuous outcomes, the recommended total sample size is 70, with 35 in each study arm with relative change in outcome variables within 95% confidence interval [41].

### Data management

Upon enrollment, each participant will be assigned a unique numeric study number so that they can be tracked anonymously throughout the study and only the Principal Investigator will have access to identifiers that can link the data to the individual participant. Consent forms and hardcopy data collection forms will be stored in a locked cabinet at the research centre and access to them is only made available through the Principal Investigator or trial coordinator.

All research data will be entered into electronic database. Two databases will be created: (1) administrative database which is a Microsoft Excel spreadsheet to compile data related to administrative matters and documentation process. They include identification data, administrative data and regulatory data and, (2) research database which includes a compilation of data that will be used for statistical analysis and outcome measures. This will encompass background data and research data. For this research database, data will be entered directly into Statistical Package for Social Sciences (SPSS) version 23.0 for ease of statistical analysis and the SPSS dataset will be duplicated onto Excel Spreadsheet to facilitate tracking of duplicate, missing and invalid values. For both databases, they will be secure and encrypted with password protection on an external hard drive. Access to the hard drive and password will only be available to Principal Investigator, delegated data manager and data entry staff.

To ensure the accuracy of the research data, three levels of data monitoring will be conducted whereby at the first level, the delegated data manager will check the hardcopies of the data collection forms to ensure accurate scoring. At the second level, data will be entered and at the third level, entries will be checked and approved by the delegated data manager.

### Biomarkers analyses and statistical analyses plan

In the analyses of the biomarkers, aliquoted plasma will be used to measure the cytokines and metabolic profiles of the research participants using single-analyte enzyme-linked immunosorbent assay (ELISA). Using targeted approach, selected RNA targets, which may include messenger RNA and micro-RNA, for a subset of the subject will be analysed based on the data obtained from the cytokines and metabolic profiles. Whole bloods aliquoted on Trucount tubes are stained with a series of fluorescence-conjugated antibodies marking the surface receptors of immune cell. Using flow cytometer, part of the phenotyping includes classical markers of senescence, Cluster of differentiation 57 (CD57) and Killer-cell lectin like receptor G1 (KLRG1), exhaustion of T cells, Programmed cell death protein 1 (PD1) and potentially identification of subpopulations of B cells and myeloid cells with a focus on the pro-inflammatory cells. The extent of DNA damage repair will be assessed by flow cytometry as well. Other immuno-assays aiming at identifying markers or predictors of immune status to examine the effects of the interventions may be applied with the bio-banked samples.

In the data analyses procedures, statistical significance level will be set at .05 for all descriptive and statistical analyses. All analyses will be performed using the SPSS. Based on the initial condition assignment and using the last observation carried forward (LOCF) method, intention-to-treat analyses will be conducted. Preliminary analyses will be performed next to assess the influence of demographic factors that (age, gender, education level, marital status, etc.). Where necessary, these variables will be included as covariates or control variables in the analyses. As some attrition is expected between interviews, prior to data analysis, comparisons will be made of retained and non-retained participants, to determine whether there are any systematic differences.

If there are chance imbalances in baseline participants’ characteristics, they will be entered as covariates in the analyses. Repeated Measure Analysis of Variance (ANOVA) will be used to examine the difference of the outcome between the active treatment group and waitlist control group over the 3 time points [42]. If there are imbalances in baseline participants’ characteristics, those variables will be included as covariates in the analyses. Additionally, dependent t-test will be employed to analyse the changes in scores within the active treatment group across the 3 time-points.

Ratios of selected biomarkers will be taken between cortisol, IL-6, CRP and DHEA-S. Additionally, fold changes and percentage changes would be performed. In the case of significant difference between the baseline measurements of prognostic demographic variables, multivariate regression will be performed when examining the differences between the means of the biomarkers for the two study arms. Correlation and/or heatmap analyses will be carried out to examine the relationships between the biomarker levels. On the aggregate biomarker level, principal component analyses (PCA) will be performed to examine the overall effect of the treatment. Mediational analyses employing bootstrapping technique will be employed to explore the mediating variables between the psychometric outcomes and biomarker levels.

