Because the present study is a goal-oriented intervention which seeks to enhance the mental, cognitive and physical health of the elderly participants, the definition put forth is adopted:

“Horticultural therapy (HT) is a professionally conducted client-centered treatment modality that utilizes horticulture activities to meet specific therapeutic or rehabilitative goals of its participants. The focus is to maximize social, cognitive, physical and/or psychological functioning and/or to enhance general health and wellness (p. 5).” [11].

Enhanced with the environmental benefits offered by the nature, HT may be a promising intervention in promoting public health and critical in prevention work. However, there is currently a paucity of research on the effectiveness of HT in a multi-ethnic Singaporean population as most studies were conducted either on western societies [6, 12, 13] or Japan and Korea [14]. Due to unique social and cultural specificities, it is inappropriate to assume that the findings could be generalized to our local population.

Furthermore, there are limitations in the existing research. Most of the other studies either have small sample sizes [15–17], short intervention duration [8, 18], or employed the sole use of questionnaires without collaborating evidence from biological data. In addition, a systematic review found that the randomized controlled trials (RCT) conducted thus far have poor methodological and reporting quality [19]. Further research is therefore needed to determine the effectiveness of HT in improving the health of the elderly in the multi-ethnic Singaporean community.

Therefore the aims of this study are to investigate the effectiveness of HT in improving the mental, cognitive and physical health of the community-dwelling older adults using a RCT design. Based on the existing literature, it was hypothesized that, as compared to the waitlist control, participants in the active treatment group will 1) have better mental health, 3) have greater improvement of cognitive functioning and 3) have better physical health. In order to have collaborative evidence with measures of psychological health, the immunology of participants will be investigated via blood-based biomarkers. Notably, past research has found that depressive symptomatology was associated with elevated levels of pro-inflammatory cytokines [20] and lower levels of trophic factor [21].

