## Discussion

This RCT study has been designed to test the effectiveness of HT in improving the mental, cognitive and physical health of the older adults. Studies have shown that contact with nature has been associated with positive mood and improved sleep quality [13] and HT which allows for engagement with nature has been suggested to mitigate stress and improve mood state [7]. This study will be conducted on a multi-racial Asian population to provide substantiation if HT can improve mental health, cognitive functioning or physical health. With the objective measures of biomarkers as collaborative evidence, the proposed study will make significant contributions, both to a theoretical understanding of mental and cognitive health and to providing needed information to the healthcare providers coping with an ageing population.

In addition, this study is evaluating not only quantitative data but also qualitative data via feedback questionnaire. This will provide information on the subjective experience of the participants, and to inform areas of improvement for future programs as ultimately our focus will be on the benefits to the individual and the opportunities to continue such a program beyond the duration of the project.

HT may offer a playful and enjoyable experience to the participants, thereby providing an intrinsic motivation and increasing compliance. Hence, older adults would be self-motivated to appreciate nature and be engaged in gardening even after the program ends. As a basic premise of this community-based initiative, we seek to build the capacity of the participants and empower them to take charge of their own health. This change in lifestyle will enhance their physical activity levels, and consequently increasing their health and ability to cope more effectively with the challenges faced in their daily life.

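### No primary outcome is named and about 22 outcomes are each tested at .05, so if HT has no effect the chance of at least one nominally significant result is about 44% to 68% (assumed common correlation 0.5 to 0)

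*Protocol article*

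**What the plan says.** The section on biomarker and statistical analyses sets one threshold for everything: "statistical significance level will be set at .05 for all descriptive and statistical analyses". It then says that "Repeated Measure Analysis of Variance (ANOVA) will be used to examine the difference of the outcome" between arms over three time points, without saying which outcome is meant. Within-arm paired t-tests, biomarker ratios, fold changes, principal components and mediation analyses are added.

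The Background predicts that participants given HT "will 1) have better mental health, 3) have greater improvement of cognitive functioning and 3) have better physical health" than the waitlist. The three hypotheses are not ranked. The Discussion says "This RCT study has been designed to test the effectiveness of HT in improving the mental, cognitive and physical health", and a few sentences later joins the three domains by 'or', so that success in any one would seem to count.

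The Sample size section reads: "For a pilot RCT with continuous outcomes, the recommended total sample size is 70, with 35 in each study arm". It gives no effect size, standard deviation or power. Nowhere does the article name a primary outcome, a primary time point or a multiplicity adjustment.

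**The concern.** A single threshold applied to every outcome, with none ranked, lets whichever outcome reaches .05 be presented as support for one of the three hypotheses. Nothing in the article says which result would confirm or refute better mental health, for example, when five scales and six blood markers all bear on it. The stated error rate of 5% then applies to each test, not to the conclusion that HT works.

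The article adds to the difficulty by describing the trial in two ways. A pilot size suits estimation and planning. A test of effectiveness in three domains calls for a stated decision rule. The Discussion expects the results to inform healthcare providers, so an undefined success criterion would carry weight beyond a pilot. The Study progress section reports data collection complete and analysis under way, which leaves little time for a credible prespecification.

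**Working it through.** **The plan's own figure.** 2 × 35 = 70, which is consistent. It cannot be derived further, because no effect size, standard deviation, power or precision target is given.

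**Count of outcomes, one score each, from the Assessment subsections.**
- Psychometric scales: SDS, SAS, Ryff, SWLS, Friendship Scale = 5
- Named blood markers: IL-6, IL-1β, CRP, cortisol, BDNF, DHEAS = 6
- Cognitive instruments: CDR, MoCA, RAVLT, Digit Span, Colour Trails, Block Design, Semantic Fluency = 7
- Physical measures: blood pressure (counted once), pulse, height, weight = 4

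Total 5 + 6 + 7 + 4 = 22. Height is not a plausible treatment outcome, and without it 21 remain. The blood markers are described as corroborating the self-reports. Without height and those six, 22 − 1 − 6 = 15 remain. Not counted are RAVLT and Ryff subscores, marker ratios, flow-cytometry and RNA markers, and the within-arm tests.

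**Assumptions.** Sidedness is not stated. The ANOVA F test has no direction, so each test is taken as two-sided at .05. The correlation between outcomes is not in the document. A common value r is assumed and varied.

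**Chance of at least one p < .05 if HT affects nothing.**
- Independent: 1 − 0.95^k. For k = 22, 1 − 0.3235 = 0.676. For k = 15, 1 − 0.4633 = 0.537.
- Correlated: 1 − ∫ φ(u) [Φ((c − √r·u)/√(1−r)) − Φ((−c − √r·u)/√(1−r))]^k du, with c = 1.96, integrated numerically.
- Results favouring HT only: .025 per test. Independent, 1 − 0.975^k; for k = 22, 1 − 0.5729 = 0.427. Correlated, the same integral with the upper limit only.

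| Outcomes | r = 0 | r = 0.3 | r = 0.5 |
|---|---|---|---|
| 22, either direction | 67.6% | 56.9% | 43.9% |
| 21, either direction | 65.9% | 55.5% | 42.9% |
| 15, either direction | 53.7% | 45.7% | 36.1% |
| 22, favouring HT only | 42.7% | 29.6% | 22.1% |

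For 22 outcomes the two-sided figure falls below 40% at r of about 0.56, and is 30.1% at r = 0.7 and 15.9% at r = 0.9. With different correlations within and between the four groups of outcomes, simulation gives 57.2% at 0.5 within and 0.1 between, and 47.3% at 0.7 and 0.2.

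**The narrowest reading.** The five psychometric scales alone, either direction: 1 − 0.95^5 = 22.6% if independent and 18.3% at r = 0.5.

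**The case against.** **A hierarchy may exist elsewhere.** The registry entry, the full protocol or an analysis plan may name a primary outcome, and none of them is shown. That limits the statement to this article. It does not remove the point, because the article goes beyond silence and affirmatively applies .05 to all analyses.

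**The pilot status is disclosed.** The Sample size section uses the word, the Discussion speaks of guiding larger trials, and the mediation analyses are called exploratory. This stands in part, and makes the conflict between sizing and aim a matter of wording. It does not supply a decision rule.

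**The count of 22 is generous.** Height and the corroborating markers can fairly be left out. With 15 outcomes the figures fall but stay far above 5%.

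**Stronger readings that the documents do not support.**
- A reader might infer that a claim that HT works has more than a 40% chance of being false. That reverses the conditional. It needs a prior probability and power, and the article gives neither. With a family-wise error of 0.5 and an assumed 95% chance of a significant result when HT works, p × 0.5 / [p × 0.5 + (1 − p) × 0.95] gives 11.6%, 34.5% or 55.1% for a prior probability of no effect p of 0.2, 0.5 or 0.7.
- A reader might infer that a significant benefit is likelier than not under no effect. For 22 outcomes, results favouring HT reach at most about 43% on the assumed correlations.
- A reader might blame the pilot size for the error rate. Sample size limits power; it does not raise family-wise error.
- A reader might infer that 35 per arm detects only large effects. An unadjusted two-sample t-test has 80% power at 0.68 SD, but the plan uses repeated measures. With baseline adjustment and an assumed baseline-to-follow-up correlation of 0.5 to 0.7, 0.679 × √(1 − 0.5²) = 0.59 and 0.679 × √(1 − 0.7²) = 0.48. Both ignore dropout, although "some attrition is expected between interviews". No power figure is relied on here.

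**Conclusion.** The point holds as a statement about error rates. The article tests every outcome at .05, ranks none, and presents an effectiveness test in three domains on a pilot size. If HT affects nothing, the chance of at least one nominally significant result among about 22 outcomes is 68%, 57% or 44% at an assumed common correlation of 0, 0.3 or 0.5. For 15 outcomes it is 54%, 46% or 36%. For results favouring HT among 22, it is 43%, 30% or 22%, still more than four times the nominal 5%. The size depends on which outcomes are counted and on a correlation that the article does not give. The absence of a primary outcome and of an adjustment does not depend on either.

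**What to change.** First establish and record whether anyone has viewed results by arm.

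- **If not viewed:** name one primary outcome with its time point or contrast, dated and shown to precede access to results by arm, and tested at two-sided .05. The SDS total is one candidate, because the Trial design section bases the assessment schedule on depressive symptoms. That section supports both 3 and 6 months and singles out neither, so the contrast must be chosen and defined within the planned repeated-measures model. Treat all other psychometric, cognitive, physical and biomarker results as secondary or exploratory, with Holm or false-discovery-rate control, or with no confirmatory claim. Holm applied separately in three domains beside a primary at .05 does not control error overall: across four families it allows up to 1 − 0.95^4 = 18.5% if they are independent. The scope of any control should therefore be stated.
- **If viewed:** label every outcome exploratory.
- **In either case:** describe the trial as a pilot throughout, and reconcile the Sample size section with the aims in the Background and Discussion.

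The cost is a change of wording and a dated record of the choice. The downside is fewer nominally significant results and a more modest stated aim.

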### Trial design

This interventional study will be a RCT comparing participation in a HT program to being in a waitlist control. The intervention will lasts for 6 months with 1-h HT sessions during the first 3 months followed by monthly sessions the next 3 months. Outcome assessments will be conducted at baseline, 3 months and 6 months. The 3-months follow-up intervals were decided based on a study by Gonzalez et al. which found that participants’ depressive symptoms declined after 3 months and these improvements were maintained in the final 6-month follow-up [6].

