### Intervention

The HT intervention is delivered in 1-h sessions, weekly in the first 3 months, followed by monthly sessions for the next 3 months (see Table 1). The extension of monthly sessions for 3 months is to determine sustainability and longer-term changes. Conducted by a trained practitioner and volunteer facilitators, the intervention is designed to cultivate an interest in gardening and promote relaxation. The participants will be assigned into groups of 7 with a facilitator for enhanced personal engagement. The participants will be with the same group members and facilitator throughout the intervention in order to build rapport and social connectedness. The facilitators are volunteers with the National Parks Board, who were trained with some basic knowledge of horticultural skills such as plant propagation, plant identification, flower arranging, houseplant care, and horticulture crafts. The essential element of the HT program is to communicate to the participants that plants are living things that must be given care. This caring extends the emotional growth of the participants.

**Table 1 Tab1:** Planned activity sessions for the 6 months of intervention

Session	Topic	Activity	Venue
1	Introduction	1. Familiarisation with research centre 2. Group formation 7/group 3. Indoor Gardening basics	Research Centre
2	Introduction	1. Garden familiarisation 2. Vegetables growing brief 3. Sowing vegetables seedlings	Chinese Garden
3	Wetland Walk	1. Park amenities familiarization 2. Interpretive walk 3. Reflection	Sungei Buloh Reserve
4	Introduction	1. Briefing for vegetables maintenance 2. Weeding and fertilizing vegetables plot	Chinese Garden
5	Nurturing	1. Briefing on pressed flowers 2. Material preparation 3. Make pressed flowers card	Research Centre
6	Nurturing	1. Garden maintenance briefing 2. Weeding, pruning, mulching garden/vegetables	Chinese Garden
7	Colour Walk	1. Park amenities familiarization 2. Interpretive walk 3. Reflection	Singapore Botanical Gardens
8	Nurturing	1. Vegetables maintenance 2. Compost making brief 3. Make compost	Chinese Garden
9	Harvest and Cook	1. Harvest vegetables 2. Hands on preparation for food 3. Sharing of cooked vegetables	Research Centre
10	Harvest and Cook	1. Seed sowing 2. Herbal plant brief 3. Herbal plants propagation	Chinese Garden
11	Festive Walk	1. Park amenities familiarization 2. Interpretive walk 3. Reflection	Gardens by the Bay (Flower Dome)

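### LOCF is the only stated handling of missing visits, although attrition is expected; it can bias the month-6 effect in either direction and should not be the primary method

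*Protocol article*

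**What the plan says.** The schedule has three visits: "Outcome assessments will be conducted at baseline, 3 months and 6 months" (Trial design). The section on biomarker and statistical analyses fixes the missing-data rule: "Based on the initial condition assignment and using the last observation carried forward (LOCF) method, intention-to-treat analyses will be conducted". The same section anticipates loss, "As some attrition is expected between interviews", and its only other response is descriptive: "comparisons will be made of retained and non-retained participants, to determine whether there are any systematic differences". That step may reveal selective drop-out but corrects nothing.

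The completed data then enter two analyses. Between arms, "Repeated Measure Analysis of Variance (ANOVA) will be used to examine the difference of the outcome", over all three time points. Within the HT arm, "dependent t-test will be employed to analyse the changes in scores within the active treatment group across the 3 time-points". The Intervention section gives the second half of the programme its own purpose: "The extension of monthly sessions for 3 months is to determine sustainability and longer-term changes". The article states no attrition rate and no assumption under which LOCF would be acceptable.

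**The concern.** LOCF treats a copied value as an observed one. Anyone lost before month 3 is analysed with no change from baseline at either follow-up. Anyone lost between months 3 and 6 is analysed with no change over exactly the period meant to show whether benefit lasts. Neither is a natural assumption for mood scales, cognitive tests that improve with repetition, or blood markers.

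At stake are the size of the month-6 contrast and the reading of sustainability. Because the article names the method, this is a stated choice and not a detail left to a fuller document.

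**Working it through.** **Inputs.** From the article: visits at baseline, month 3 and month 6; 35 participants per arm; LOCF; attrition expected but not quantified. There is no attrition or effect figure to reproduce. Drop-out shares, effects and drift below are assumptions, in SD units, with positive meaning benefit.

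**Formula, equal and completely random loss.** Let d1 be the share lost before month 3, d2 the share lost between months 3 and 6, and E3 and E6 the true between-arm effects. Completers contribute E6, late losses E3 and early losses 0. Any drift common to both arms cancels.

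- Expected LOCF effect at month 6 = (1 − d1 − d2)·E6 + d2·E3
- Bias = d2·(E3 − E6) − d1·E6

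| E3, E6 | d1 | d2 | LOCF effect at month 6 | Bias |
|---|---|---|---|---|
| 0.5, 0 | 0 | 5% | 0.05 × 0.5 = 0.025 | +0.025 |
| 0.5, 0 | 0 | 10% | 0.10 × 0.5 = 0.05 | +0.05 |
| 0.5, 0 | 0 | 20% | 0.20 × 0.5 = 0.10 | +0.10 |
| 0.5, 0.25 | 0 | 10% | 0.90 × 0.25 + 0.10 × 0.5 = 0.275 | +0.025 |
| 0.5, 0.25 | 0 | 20% | 0.80 × 0.25 + 0.20 × 0.5 = 0.30 | +0.05 |
| 0.5, 0.5 | 5% | 0 | 0.95 × 0.5 = 0.475 | −0.025 |
| 0.5, 0.5 | 10% | 0 | 0.90 × 0.5 = 0.45 | −0.05 |
| 0.5, 0.5 | 20% | 0 | 0.80 × 0.5 = 0.40 | −0.10 |
| 0.3, 0.5 | 0 | 20% | 0.80 × 0.5 + 0.20 × 0.3 = 0.46 | −0.04 |
| 0.5, 0.5 | 0 | 20% | 0.80 × 0.5 + 0.20 × 0.5 = 0.50 | 0 |
| 0.5, 0.25 | 10% | 10% | 0.80 × 0.25 + 0.10 × 0.5 = 0.25 | 0 |

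Early loss dilutes a real effect. Late loss flatters a fading effect and understates a growing one. The last two rows show zero bias: a constant effect with no early loss, and two terms that cancel. With no effect at either visit and equal loss, the bias is also zero.

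**Within the HT arm.** Every lost participant has a month 3-to-6 change of zero, so the expected mean change is (1 − d1 − d2) times the true one. With no early loss and 20% late loss, that is 80% of it.

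**Unequal loss with common drift.** With no treatment effect, early loss only, and a drift c in both arms by month 6, the LOCF difference is c × (waitlist loss − HT loss).

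- c = 0.3, HT 10%, waitlist 30%: 0.3 × 0.20 = +0.06
- c = 0.4, HT 20%, waitlist 5%: 0.4 × (−0.15) = −0.06

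The sign depends on which arm loses more.

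**Check by simulation.** 35 per arm, between-visit correlation 0.6, E3 = 0.5, 5% early loss, then 20% of those still in lost before month 6, 4,000 runs. The comparator is a likelihood-type estimate from sequential regressions.

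| True E6 | LOCF, random loss | LOCF, loss depending on month 3 | Likelihood-type, same two cases |
|---|---|---|---|
| 0 | 0.104 | 0.081 | 0.009, −0.001 |
| 0.25 | 0.283 | 0.273 | 0.248, 0.243 |
| 0.50 | 0.475 | 0.475 | 0.498, 0.503 |

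**Scale.** For an unadjusted difference at one visit with 35 per arm, the 95% confidence half-width is 1.96 × √(2/35) = 0.47 SD.

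**The case against.** The strongest defence is that the bias may be small or absent here. HT sessions continue monthly to month 6, so that visit is still on treatment. The Trial design section justifies the three-month intervals by a cited study in which improvement at 3 months was maintained at 6. On that premise E3 is close to E6, and late loss adds almost no bias to the arm contrast. The article gives no attrition rate, and loss may be low. This is a pilot-sized trial whose confidence interval is several times wider than the biases above. If the effect is constant and loss is equal, the bias runs against HT.

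All of this stands as a limit on size. It does not rescue the method: a stable effect is part of what months 3 to 6 are meant to test, so the missing-data rule should not presuppose it. Nor does a constant effect protect against early loss.

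A reader might also infer more than the article supports:

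- That LOCF is biased whenever anyone drops out, or valid only if every individual score freezes. The formula shows zero bias in the arm contrast in several cases without frozen scores.
- That a sustained effect at month 6 would be an artefact. Zero change is certain only for the copied values; the arm contrast looks falsely maintained only if the true effect fades.
- That the bias always dilutes HT. Its direction depends on when participants are lost, how the effect evolves, and whether the arms lose equally.

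**Conclusion.** The point holds in conditional form. The article fixes LOCF as its sole treatment of missing visits while expecting some. Under equal, completely random loss, the month-6 bias of d2(E3 − E6) − d1·E6 is zero only in special cases that the article does not claim. Unequal loss combined with common drift can create a difference of either sign where none exists.

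With an assumed month-3 effect of 0.5 SD and one-sided timing of loss (all early or all late) of 5% to 20%, the bias ranges from −0.10 SD (constant effect, 20% early loss) to +0.10 SD (vanished effect, 20% late loss). That is at most about a fifth of the confidence half-width (0.10/0.47 = 0.21). The matter should be fixed, but on these figures it does not by itself invalidate the trial. The sizes rest entirely on assumed drop-out, effects and drift.

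**What to change.** Replace LOCF as the primary method by one of two options, keeping participants in their allocated arm:

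- A likelihood-based mixed model for repeated measures on all observed data, with arm, visit, arm-by-visit, baseline and the stratification factor gender. The MIXED procedure in SPSS, the package already named, fits it.
- Multiple imputation under missing at random, using the same variables.

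Add one sensitivity analysis for departures from missing at random. Keep LOCF at most as a secondary check. Keep the comparison of retained and non-retained participants as description, reported by arm and by timing of loss so that d1 and d2 are visible.

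The cost is revised wording and a few lines of code, with no new data. The method then relies on missing at random, which cannot be verified and is why the sensitivity analysis is needed. In a model with baseline as a covariate, participants with no follow-up visit contribute no outcome, so their number should be reported. The Study progress section says data collection is complete and analyses are under way. The change must therefore be documented as made after data collection, stating whether results by arm were known at that point.
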